## Analysis plan

|                                                                               |  |                 |                                                                                                      |
|-------------------------------------------------------------------------------|--|-----------------|------------------------------------------------------------------------------------------------------|
| CNS                                                                    |  | All codes below | We will also compute estimates for overall CNS cancer and present if there is not power for subtypes |
| Meningioma                                                                    |  | “C70”           |                                                                                                      |
| Cancer of the brain, hypophysis, corpus pineale and ductus craniopharyngealis |  | “C71”           | If power is sufficient, we will look at glioma separately.                                           |
| Spinal cord, cranial nerve or other CNS tumours                               |  | “C72”           |                                                                                                      |

CNS: central nervous system

Note: All subcodes are included unless otherwise stated

### Follow-up

- Follow-up start: index date.
- Follow-up end: earliest of emigration, death, end of study (30 June 2017) or first-ever cancer diagnosis (when examining specific cancers, patients are thus censored if diagnosed with another individual cancer).
- If a person from the comparison cohort is diagnosed with eczema during follow-up, that person will be censored at time of diagnosis. The person will then contribute to the eczema cohort together with his/her own comparators (this has been accounted for in the sampling done by the Danish Health Data Authority)

### Covariables

We will include various variables, shown in table 3. With the exception of socioeconomic variables, variables are time-updated. Thus, people will contribute person-time in the unexposed category for a given variable until they fulfill the definition for the condition/treatment, after which they will contribute in the exposed category for the remaining follow-up.

**Table 3.** Covariables

| ICD-8 | ICD-10 | Other codes in patient registry | ATC | Notes |
|-------|--------|---------------------------------|-----|-------|
|-------|--------|---------------------------------|-----|-------|

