## Analysis plan

### *Eczema exposed*

- Persons with a diagnosis of atopic eczema (ICD-8: 691; ICD-10: DL20) in the Danish National Patient Registry between 1 Jan 1977 and 10 February 2018.
- We include all primary and secondary diagnoses for eczema from admissions, hospital outpatient clinics and emergency rooms in the Danish National Patient Registry, including ongoing contacts (that is, persons who at the end of study period are in active follow-up in a hospital outpatient clinic).
- Index date = The earliest hospital record for atopic eczema (date of admission or first outpatient appointment).
- Only persons who are born in Denmark and living in Denmark on the index date (i.e. date of first record for eczema).

For the current study, we will further restrict the study population as follows:

- We will exclude eczema patients (together with their matched comparators) identified by an ICD-8 diagnosis recorded together with an additional (“modification”) code indicating that it potentially an uncertain/unverified/working diagnosis (c\_diagmod=1–7).
- We will exclude patients (together with their matched comparators) with inconsistencies in registration of status and residence in the Civil Registration System (recorded as alive but not living in Denmark but without an emigration date), as we assume that these patients are not living in Denmark and thus not eligible.
- To ensure that we have at least 1 year of registration history from included registries (except the prescription registry), we will only include patients (together with their matched comparators) with index date on 1 January 1982 or later. In the subanalysis on severity and in a sensitivity analysis, we restrict to those diagnosed on 1 January 1996 or later in order to ensure one year of registration history in all databases.
- To ensure at least 1 year of follow-up after start of eligible follow-up (available until 30 June 2017), we will include eczema patients until 30 June 2016.
- We will exclude eczema patients (together with their matched comparators) with a record for any cancer (except non-melanoma skin cancer) before or on index date (see Table 2). That is, we will not only exclude those with history of the cancer outcome of interest. However, in analyses of non-melanoma skin cancer specifically, we will exclude those with previous history of this cancer as well.

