### *Unexposed cohort*

- Up to 10 persons matched to each eczema patient by sex and birth year.
- Comparators have to: (1) be born in Denmark, (2) be alive and living in Denmark on the on index date of their matched eczema-exposed individual (i.e. first hospital eczema diagnosis), and (3) have no previous diagnosis of eczema.
- Index date = The same index date as their matched eczema-exposed individual

As with eczema patients, we will additionally apply the following restrictions:

- We will exclude matched comparators with inconsistencies in registration of status and residence in the Civil Registration System (recorded as alive but not living in Denmark but without an emigration date), as we assume that these patients are not living in Denmark and thus not eligible.
- We will exclude comparators with any cancer (except non-melanoma skin cancer) before or on index date (see Table 2). That is, we will not only exclude those with history of the cancer outcome of interest. However, in analyses of non-melanoma skin cancer specifically, we will exclude those with previous history of this cancer as well.

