|                                                                                                    |                  | "DC94" "DC95"
"DC81" "DC82"
"DC83" "DC84"
"DC85" "DC86"
"DC88" "DC96"           |                                        |
| Use of oral corticosteroids                                                                        |                  | "H02AB" and
DOSFOR M "TAB"
or
"TABMO D"                                            | Any prescription excluding injections. |
| Systemic treatment for eczema (cyclosporine, azathioprine, mycophenolate, methotrexate, dupilumab) | Procedure codes: | "L04AX0 1"
"BOHJ18 B8"
"BWHB83 3"
"BWAH1 15"
"BOHJ20"
"BOHJ22"
"D11AH0 5" |                                        |
| Asthma                                                                                             | "493"            | "DJ45" "DJ46"                                                                               |                                        |

Note: All subcodes are included unless otherwise stated; all types of contacts (inpatient, outpatient and emergency) and both primary and secondary diagnoses should be considered. Use admission/prescription/record date for all variables.

aBaseline information only

bDocumentation is available here:

<https://www.dst.dk/da/Statistik/dokumentation/Times/forskningsservice/efalle>

<https://www.dst.dk/da/Statistik/dokumentation/Times/cpr-oplysninger/c-faelle-id>

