## Analysis plan

3. With time since index date as underlying time scale, we will use stratified Cox regression (conditioning on matched set) to compute unadjusted hazard ratios (99% confidence intervals) to determine associations between eczema and each outcome (that is, comparing eczema patients and the comparison cohort). By stratifying on matched set, the model accounts for birth year, sex and calendar period. We will then fit a “mediation model” additionally adjusting for time-varying lifestyle-related diseases (chronic obstructive pulmonary disease, hyperlipidemia, hypertension, alcohol-related conditions, ischemic heart disease, hospital-diagnosed obesity and type II diabetes). If sufficient power, we will adjust for the lifestyle-related diseases as individual variables.

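### Secondary codes given at eczema contacts can switch on lifestyle diseases, and only the exposed have such contacts, so the mediation model is open to differential covariable recording

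*Protocol*

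**What the plan says.** Apart from the socioeconomic variables, covariables are time-updated and irreversible: "people will contribute person-time in the unexposed category for a given variable until they fulfill the definition for the condition/treatment", after which they stay in the exposed category (Protocol, Covariables). The note under Table 3 says that "all types of contacts (inpatient, outpatient and emergency) and both primary and secondary diagnoses should be considered", dated at admission, prescription or record. Contacts for eczema are not excepted.

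The two cohorts enter differently. For eczema patients, "Index date = The earliest hospital record for atopic eczema (date of admission or first outpatient appointment" (Eczema exposed). For comparators, "Index date = The same index date as their matched eczema-exposed individual" (Unexposed cohort). They must be born, alive and living in Denmark and "have no previous diagnosis of eczema". They are matched on sex and birth year, and no hospital contact is required. Under Follow-up, "If a person from the comparison cohort is diagnosed with eczema during follow-up, that person will be censored at time of diagnosis".

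The covariables enter the second model of Statistical analyses, item 3: "We will then fit a “mediation model” additionally adjusting for time-varying lifestyle-related diseases". That model has a column in every hazard ratio table. The same diseases appear as baseline rows in Table 1.

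**The concern.** Every exposed person has at least one hospital contact at time zero, and some have further eczema contacts later. At each of these a clinician may also code COPD, obesity, hypertension or another listed disease as a secondary diagnosis, and Table 3 counts that code permanently. Unexposed person-time in the main analysis contains no eczema contacts, so it lacks this recording opportunity. The difference comes from how exposure is defined.

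If the extra opportunity means fuller recording in the exposed, a disease that raises cancer risk will look commoner in eczema patients even when true prevalence is equal. The model then assigns part of the eczema association to the disease, and the fall from the unadjusted to the mediation HR looks like mediation. Lung cancer adjusted for COPD is the obvious candidate. The Table 1 comorbidity rows would be affected too, through the index contact, if codes dated on the index date count as baseline.

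**Working it through.** The protocol gives no sample size, event count or recording sensitivity, so there is no figure of its own to reproduce. The check has two parts: where the asymmetry can act, and how large its effect could be.

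**Where it can act (Data sources; Table 3)**

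- Hyperlipidemia, hypertension, alcohol-related conditions and type II diabetes can also be switched on by prescriptions. That route is the same in both cohorts and starts with the Prescription Registry in 1995.
- COPD, ischemic heart disease and obesity rest on hospital records alone.
- Index dates start in 1982. Before 1995 the Patient Registry holds inpatients only, and there are no prescriptions. Every exposed person indexed from 1982 to 1994 was therefore an inpatient at time zero, and none of the seven diseases then had a prescription route.

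**Whether a planned analysis isolates it**

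- The 3-year delayed start (item 9) targets reverse causality, and a covariable already switched on stays on.
- The restriction to index dates from 1996 (item 13) secures prescription history but gives the three hospital-only diseases no new route.
- Items 16 and 17 address ascertainment of skin cancer as an outcome, not of covariables.

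**How large it could be**

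From the document: up to 10 comparators per patient, so person-time is taken as 1 exposed to 10 unexposed. All other inputs are assumptions: true prevalence p = 0.10 in both cohorts (so no real mediation), true eczema HR 1.20, perfect specificity, sensitivity s0 = 0.40 in comparators and s1 in the exposed, and covariate HR R = 2 or 4. The baseline rate is set to 1.

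- Recorded stratum: person-time n·p·s, events n·p·s·h·R.
- Unrecorded stratum: person-time n·(1 − p·s), events n·h·[(1 − p) + p(1 − s)R].
- Here n is 1 or 10, and h is 1.20 (exposed) or 1 (unexposed).
- Adjusted HR, as a Mantel-Haenszel rate ratio: Σ(A1·T0/T) / Σ(A0·T1/T), where A is events and T person-time.

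Example with s1 = 0.60 and R = 2:

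- Recorded: T1 = 0.06, A1 = 0.06 × 1.2 × 2 = 0.144; T0 = 0.40, A0 = 0.80.
- Unrecorded: T1 = 0.94, A1 = 1.2 × (0.90 + 0.04 × 2) = 1.176; T0 = 9.6, A0 = 10 × (0.90 + 0.06 × 2) = 10.2.
- Numerator: 0.144 × 0.40/0.46 + 1.176 × 9.6/10.54 = 0.1252 + 1.0711 = 1.1963.
- Denominator: 0.80 × 0.06/0.46 + 10.2 × 0.94/10.54 = 0.1043 + 0.9097 = 1.0140.
- Adjusted HR = 1.1963/1.0140 = 1.180. The crude HR is (0.144 + 1.176)/[(0.80 + 10.2)/10] = 1.32/1.10 = 1.20.

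| Exposed sensitivity | R = 2 | R = 4 |
|---|---|---|
| 40% (equal recording) | 1.200 | 1.200 |
| 45% | 1.195 | 1.187 |
| 60% | 1.180 | 1.150 |
| 70% | 1.170 | 1.126 |

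The share of the excess apparently explained is (1.20 − adjusted HR)/0.20: about 3% to 6% at 45%, 10% to 25% at 60%, and 15% to 37% at 70%.

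**When mediation is real**

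A Poisson model with prevalence 30% in the exposed and 20% in comparators, covariate HR 2 and no direct effect has a crude HR of 1.30/1.20 = 1.083 and a correct adjusted HR of 1.000. With 50% sensitivity in both cohorts the adjusted HR is 1.045. Raising exposed sensitivity to 60% gives 1.023, and to 75% gives 0.991. Equal under-recording thus understates mediation, and a modest differential moves the estimate towards the truth before overshooting.

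**The case against.** A reader might infer that lifestyle diseases are recorded more completely in eczema patients and that the mediation model will therefore show mediation that does not exist. The document does not support that much. It gives no figure for secondary coding at eczema contacts. Both cohorts collect codes from all other hospital care, with registry data from 1977, so eczema contacts only add to a common base. Four of the seven diseases have a prescription route from 1995. Going from 40% to 60% or 70% sensitivity would require eczema contacts to capture a third to a half of otherwise unrecorded disease (20/60 to 30/60). A 5-point gap barely moves the HR. The net direction is also open when mediation is real. The protocol labels the model a mediation model but gives no proportion mediated and no rule for interpreting the attenuation. The primary aim is association, and the unadjusted HR does not use these covariables. All of this stands, and it limits the point to a vulnerability of unknown size.

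The obvious remedy also has a flaw. Eczema patients are identified from secondary as well as primary diagnoses, so an admission for COPD with eczema as a secondary code is also an eczema contact. Dropping every contact that carries an eczema code would delete genuine lifestyle-disease records in the exposed only. In the same model, if that left exposed sensitivity at 30% or 20%, the adjusted HR would be about 1.21 to 1.25, a bias in the opposite direction. Any filter must be narrower than that.

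The objection does not remove the asymmetry itself. It follows from the entry, censoring and coding rules taken together, and no planned analysis isolates it.

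**Conclusion.** The point holds as a vulnerability of the mediation column, not as a demonstrated bias. The Table 3 rules give the exposed a recording opportunity that main-analysis comparators lack, and this can create or inflate apparent mediation for diseases that raise cancer risk. The risk is greatest for COPD, ischemic heart disease and obesity, and for all seven diseases before 1995.

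Under the stated assumptions a true HR of 1.20 becomes anything from 1.195 (45% exposed sensitivity, covariate HR 2) to 1.126 (70%, covariate HR 4). Nothing in the document says where in that range the study lies, and the upper end should not be quoted as the expected effect. Real mediation with under-recording in both cohorts pulls the other way. The unadjusted HRs are unaffected.

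**What to change.** Keep the current Table 3 rule as the main one. Add one sensitivity version of the mediation column of the hazard ratio Table 2 and of the comorbidity rows of Table 1. In that version:

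- A lifestyle-disease code recorded as a secondary diagnosis at a contact where eczema is the primary diagnosis, including such an index contact, does not switch the covariable on.
- Codes from all other contacts still count, including an admission for a lifestyle disease that carries eczema as a secondary code. Prescriptions also still count.

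State in item 3 that attenuation will be read as mediation only if it is similar under both rules.

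The cost is one filter in the covariable program, one extra column in Table 2 and a second set of comorbidity rows in Table 1. The downside is that some true disease in eczema patients will be dated later or missed in the sensitivity version, which is why it should stand beside the current rule and not replace it.

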## Analysis plan

|                                                                      |                                                                   |                                                                                                                                      |                                                                                                                |
|----------------------------------------------------------------------|-------------------------------------------------------------------|--------------------------------------------------------------------------------------------------------------------------------------|----------------------------------------------------------------------------------------------------------------|
| Age                                                                  | <18
18–44
45–64
≥65 years                                |                                                                                                                                      |                                                                                                                |
| Sex                                                                  | Men
Women                                                      |                                                                                                                                      |                                                                                                                |
| Calendar period                                                      | 1982–1999
2000–2004
2005–2009
2010–2015                  |                                                                                                                                      |                                                                                                                |
| Various lifestyle-related diseases, as proxy for unhealthy lifestyle |                                                                   |                                                                                                                                      |                                                                                                                |
| Chronic obstructive pulmonary disease                                | “491”
“492”                                                    | “DJ41” “DJ42”
“DJ43” “DJ44”                                                                                                       |                                                                                                                |
| Hyperlipidemia or treatment of hyperlipidemia                        | “27200”                                                           | “DE780”                                                                                                                              | “C10”                                                                                                          |
| Hypertension or antihypertensive treatment                           | ”400”
”401”
”402”
”403”
”404”                         | ”DI10” ”DI11”
”DI12” ”DI13”
”DI14” ”DI15”
”DI674”                                                                           | “C02”
“C03”
“C07”
“C08”
“C09”                                                                      |
| Alcohol-related conditions                                           | “291”
“303”
“57109”
“57110”
“57710”
“979”
“980” | ”DF10” ”DG312”
”DG621”
”DG721” ”DI426”
”DK292”
”DK700”
”DK703”
“DK860”
“DR780”
“DT510”
“DT519”
“DZ721” | “N07BB01”                                                                                                      |
| Ischemic heart disease                                               | ”410”
”411”
”412”
”413”
”414”                         | ”DI20” ”DI21”
”DI22” ”DI23”
”DI24” ”DI25”
”DT823D”
”DT823E”                                                              | “30009” “30019”
“30029” “30039”
“30049” “30059”
“30069” “30079”
“30089” “30099”
“30109” “30119” |

|                                                                                                  |       |                |                                                  |                                                                                                                                                                                                                                                                             |
|--------------------------------------------------------------------------------------------------|-------|----------------|--------------------------------------------------|-----------------------------------------------------------------------------------------------------------------------------------------------------------------------------------------------------------------------------------------------------------------------------|
|                                                                                                  |       |                |                                                  | “30120” “30129”
“30139” “30149”
“30159” “30169”
“30179” “30189”
“30199”
“KFNA”
“KFNB”
“KFNC”
“KFND”
“KFNE”
“KFNH20”
“KFNG”
“KFNF”                                                                                                       |
| Hospital-diagnosed obesity                                                                       | “277” | “DE65” “DE66”  |                                                  |                                                                                                                                                                                                                                                                             |
| Type II diabetes                                                                                 | “250” | “DE11” “DO241” | Oral antidiabetic = “A10B” (excluding “A10BE01”) | Any type II ICD code or second prescription for oral antidiabetic                                                                                                                                                                                                           |
| Socioeconomic status (education and social registries from Statistics Denmark) a      |       |                |                                                  | For use in a sensitivity analysis among those aged 30 years or older at index date.                                                                                                                                                                                         |
| Highest attained educational level (primary education, secondary education, or higher education) |       |                |                                                  | 
 
• Short term education (7-10 years) if afsp1e code = 10
 
• Medium term education (11-12 years) if afsp1e code 20<= & <40
 
• Long term education (13+ years) if afsp1e code 40<= & <90
 
 |

